#### Identity and labeling of investigational product(s)

Prednesol® 5 mg tablets and Dexamethasone tablets 2 mg will be supplied as open label commercial stock and will be labeled and stored in accordance with the required regulatory guidelines, the Summary of Product Characteristics and hospital procedures.

#### Storage of second and third doses of prednisolone

After randomization and administration of the Day 1 dose, and prior to discharge from the ED, the parents/legal guardians of patients randomized to the prednisolone group will be instructed on how to store the remaining study drug appropriately and out of reach of children. If a patient randomized to the prednisolone group is admitted to OLCHC, a member of the research team will be responsible for supplying the prednisolone dose on Days 2 and 3. This dose will be dispensed from the study medication pack.

### Study procedure

#### General description

Before the start of the study, the research team will conduct training sessions for all ED nurses and physicians to explain roles and responsibilities and all aspects of the study. Training sessions on the PRAM score have also taken place, and this score has been used in the assessment of all asthma exacerbations (over the age of 2) presenting to the ED from April 2011 onwards.

Eligible participants will be identified at triage or during clinical consultation by the ED clinician. They and their parents/guardians will be provided with written and verbal information about the study. All patients in the study will be recruited by a member of the research team or an ED clinician.

After eligibility for inclusion in the study is confirmed, the research trial and procedures involved will also be explained to the patient in age-appropriate language. In all cases, where appropriate, informed assent will be obtained from the patient. This may not be possible in younger patients and in patients who are too unwell (for example, short of breath) to actively participate in the consent process. If the patient recovers sufficiently, we will go through the assent process with them at a later stage. In all cases without exception, informed consent will be obtained from the parent/legal guardian. If a patient refuses assent they will not be included in the study, even if a parent/legal guardian gives consent.

The informed consent process will be documented in the medical notes (including the date/time of consent and the provision of information to the patient/parent(s)/guardian). Once the patient is consented, randomization will occur.

The patient will be randomized by the recruiting clinician to receive either a stat dose of oral dexamethasone 0.3 mg/kg (max. dose 12 mg) in the ED, *or* prednisolone 1 mg/kg/day (max. dose 40 mg) for three days. The clinician will pick the next available card from a pre-randomized pack of study cards contained in a locked storage cupboard in the ED. This card will contain the study number (that is, Subject ID) of that particular patient and will state to which treatment arm they are assigned (“DEXAMETHASONE” or “PREDNISOLONE”). Subject IDs will be allocated on a consecutive basis of recruitment to the study. The patient’s weight will be checked (all patients presenting to OLCHC ED are routinely weighed after arrival unless in extremis) and the appropriate dose of study medication will then be read from the Dosing Schedule (see Table
4). The next pack of study medication with that dose will be taken. The first dose will be given in the ED by the member of the recruiting clinician. If the patient is assigned to the dexamethasone group, then this is the only dose that will be given. If the patient is assigned to the prednisolone group, the second and third doses (each dose in original foil blistered strip contained in separate labeled clear plastic zip-lock bags as described) will be given to the patient and their parent/guardian prior to discharge.

If the patient vomits the medication dose given in ED within 30 minutes of administration, a second dose will be supplied. If the patient vomits again within 30 minutes of the second dose, then no further dose will be given but the patient will remain in the study and be analyzed on an intention-to-treat basis.

Subjects and parents/legal guardians will be trained on the correct administration of prednisolone on Days 2 and 3. This training will be documented in the subject’s medical notes. Patients will be requested to bring the study packs with them for the Day 4 assessment.

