## Methods/design

### Study design and setting

This is a randomized, open-label, active control clinical trial. It will be conducted at a single tertiary urban pediatric ED (Our Lady’s Children’s Hospital Crumlin (OLCHC)) in Dublin, Ireland.

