### Patient randomization

The randomization process has been designed by CSTAR (Health Research Board Centre for Support and Training in Analysis and Research). Randomization will occur in blocks of 12 subjects. An equal number of subjects will be randomized to each treatment group for every 12 subjects enrolled.

The clinician will pick the next available envelope from a pre-randomized pack of study envelopes contained in a locked storage cupboard in the ED. This envelope will contain the study number (that is, Subject ID) of that particular patient and will contain a card which states to which treatment arm they are assigned (“DEXAMETHASONE” or “PREDNISOLONE”). Subject IDs will be allocated on a consecutive basis of recruitment to the study.

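### The article gives two incompatible descriptions of the allocation device, and a single fixed block of 12 in an open-label, one-site trial makes the difference matter

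*Protocol article*

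**What the plan says.** The allocation step is described twice in the Protocol article.

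- Study procedure, General description: "The patient will be randomized by the recruiting clinician", and "The clinician will pick the next available card from a pre-randomized pack of study cards contained in a locked storage cupboard in the ED". The card carries the Subject ID and "will state to which treatment arm they are assigned". No envelope is mentioned.
- Patient randomization: "The clinician will pick the next available envelope from a pre-randomized pack of study envelopes". Each envelope holds the Subject ID and the card naming the arm.

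Patient randomization also fixes the sequence: "Randomization will occur in blocks of 12 subjects" and "An equal number of subjects will be randomized to each treatment group for every 12 subjects enrolled". Both sections say that Subject IDs run consecutively in order of recruitment. Study design and setting adds: "This is a randomized, open-label, active control clinical trial" and "It will be conducted at a single tertiary urban pediatric ED". No strata are described, so there appears to be one sequence.

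Four other statements bear on the point. General description puts randomization after consent. It allows recruitment by the research team or by an ED clinician. Bias and confounding variables intends a blinded assessor for the primary outcome, and plans adjustment for age, asthma severity and concomitant medication if an imbalance is found. Trial Status says that recruitment ended in July 2012 and that analysis starts in September 2012.

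**The concern.** The two accounts use nearly the same sentences but differ on the one feature that decides concealment: whether the next assignment is covered when the clinician reaches for it. The article addresses this step directly and conflicts with itself, so this is not merely a detail left to a fuller document.

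The setting gives the conflict weight. Treatment is unmasked once given, the person enrolling the child also draws the assignment, and a balanced block of known length can be counted through using consecutive IDs. A recruiter who knew or could guess the next arm could choose whether to approach a given child. If sicker children were steered away from dexamethasone, mean Day 4 PRAM would look better in that arm. That would push the result towards non-inferiority against the one-point margin.

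The stated safeguards do not act on this route. Consent before randomization does not help if the next assignment is already known. The locked cupboard does not help, because recruiters draw from it. A blinded assessor protects the measurement of the outcome, not who enters each arm.

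**Working it through.** **Inputs.** Block size 12, balanced 6:6, one size (Patient randomization). Total 232, from 105 per group plus 10% (Sample size and power). Margin one PRAM point, SD 2.23 at ED discharge and 1.5 at triage (same section).

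**The plan's own figure.** The article gives no figure for predictability. Its sample size, used below as the denominator, does reproduce. With SD 2.23, margin 1, power 0.9 and one-sided 0.025 (equivalently two-sided 0.05), n = 2 × (1.960 + 1.282)² × 2.23² / 1² ≈ 105 per group. Then 105 × 1.1 = 115.5, rounded up to 116 per group, or 232.

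**Assignments certain in advance.** Take an observer who knows the block size and every earlier assignment. An assignment is certain once one arm is used up. For a block with m per arm, the expected number of certain assignments is 2m/(m + 1).

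- m = 6: 12/7 = 1.71 of 12, or 14.3%.
- Over the trial: 232 × 1/7 ≈ 33. Counting only the 19 complete blocks (232/12 = 19.3), 19 × 12/7 = 32.6, also about 33.

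**Best guessing.** The same observer always names the arm with more places left. Expected correct guesses per block are m + (4^m / C(2m, m) − 1)/2.

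- m = 6: 6 + (4096/924 − 1)/2 = 6 + 1.716 = 7.716.
- 7.716/12 = 64.3%, against 50% with no knowledge of past assignments. The certain calls are included in this figure.

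An exact recursion over all 6:6 blocks gives the same 14.3% and 64.3%.

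**How 12 compares.** Blocks of 4 would give (4/3)/4 = 33.3% certain and [2 + (16/6 − 1)/2]/4 = 70.8% guessable. Twelve is already fairly large.

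**What varying the block size would do.** With undisclosed, varying sizes an observer can rarely be certain. Guessing the under-represented arm still succeeds in simulation about 65% of the time with sizes 8 to 14 and 68% with sizes 4 to 8 (illustrative sizes). The same rule with fixed 12 gives 64%. Varying sizes remove most certain calls but do not lower the guess rate.

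**Card wording taken literally.** If the cards were uncovered in the pack, the next arm could be read whatever the block size. This depends on a physical detail that the article does not state.

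**Would a check on block ends help?** The last two positions of 19 complete blocks hold 38 children, about 19 per arm. With the triage SD of 1.5, SE = 1.5 × √(2/19) = 0.49, and the 95% interval is about ±1.96 × 0.49 = ±0.95 PRAM points. An interval that wide is close to the one-point margin itself, so a null result would not be informative.

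**The case against.** The strongest reply is that the conflict is only wording. Patient randomization is the section devoted to this step and gives the whole device: an envelope with a card in it. The general narrative names only the card, and the natural reading is shorthand. A reader might infer from that narrative that allocation was open and every assignment visible. The article does not support this: it never says that the cards were uncovered or browsable, and it places randomization after consent. Nor does the absence of words such as sealed or opaque prove anything, since an article may leave them to the full protocol. All of this stands, and it limits the point to a contradiction to be resolved.

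A reader might also infer that recruiters did foresee about a seventh of assignments. That too is unsupported. ED staff were to be trained on all aspects of the study, but the article does not say that this included the block size. Recruitment was shared among research staff and ED clinicians around the clock and at weekends, which makes complete tracking by one person less plausible. The article appeared in August 2012, after recruitment ended, so it could not have disclosed the block size to recruiters. The 14% and 64% are therefore upper bounds for a fully informed observer.

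Finally, the plan already allows adjustment for severity. It does so only if imbalance is seen, which leaves the primary model to be chosen after looking at the data.

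**Conclusion.** The point holds in limited form. The two sections contradict each other on the allocation device, and the article cannot settle which was used. One fixed block of 12, in an open-label, single-ED trial where the recruiter draws the assignment, adds a conditional weakness: at most about 14% of assignments (about 33 of 232) certain and about 64% guessable. Both figures assume knowledge of the block size and full tracking of earlier assignments.

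The documents give no evidence that anyone foresaw an assignment or acted on it. They also give no basis for putting a size on any resulting bias in Day 4 PRAM, and none is claimed. The card and envelope conflict is the stronger half, because it does not depend on what recruiters knew about blocks.

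**What to change.** 1. **Reconcile the text.** Make General description and Patient randomization describe one concealed procedure. State which device was actually used and whether recruiters knew the block size. Cost: wording and a check of trial records.

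2. **Fix the primary model now.** Before the analysis due in September 2012, prespecify triage PRAM as a covariate in the Day 4 comparison, whether or not imbalance is seen, and report triage PRAM by arm. Under General description, PRAM has been used for all asthma exacerbations over age 2 in this ED since April 2011, so no new data should be needed. This guards against chance or selective imbalance in measured severity. It does not correct selection on anything unmeasured.

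3. **Keep any block-end check descriptive.** Triage PRAM by arm in the last two positions of each block (about 38 children) may be shown, but should not be offered as reassurance.

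4. **Design lesson only.** Varying block sizes not disclosed to recruiters would have removed most certain calls, though not the guess rate. With recruitment complete, this cannot be applied here.

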### Patient randomization

The randomization process has been designed by CSTAR (Health Research Board Centre for Support and Training in Analysis and Research). Randomization will occur in blocks of 12 subjects. An equal number of subjects will be randomized to each treatment group for every 12 subjects enrolled.

The clinician will pick the next available envelope from a pre-randomized pack of study envelopes contained in a locked storage cupboard in the ED. This envelope will contain the study number (that is, Subject ID) of that particular patient and will contain a card which states to which treatment arm they are assigned (“DEXAMETHASONE” or “PREDNISOLONE”). Subject IDs will be allocated on a consecutive basis of recruitment to the study.

### Outcome measures

The outcome measures used to compare differences between the study arms will include:

Primary

PRAM score at Day 4

Secondary

Relapse rate – a relapse will be defined as any visit to a healthcare provider, for example, General Practitioner, ED, as a result of asthma symptoms within 14 days of study enrolment

Number of salbutamol therapies given following enrolment

Side effects, in particular, vomiting

Compliance with medication, assessed by interview and the return of study packs

### Statistical considerations

The aim of this study is to demonstrate that a single dose of dexamethasone is clinically non-inferior to a three-day course of prednisolone.

### Sample size and power

In this study, the Primary Variable is the PRAM Score at discharge and at Day 4 after discharge. It is assumed that the distribution of PRAM scores will take an approximate normal distribution. A change in PRAM score from 6.57 ± 1.5 (mean ± standard deviation) at triage to 2.93 ± 2.23 at discharge from ED was the basis of the validation study on PRAM (personal communication from [name])
[21]. The sample size calculation below compares dexamethasone and prednisolone at Day 4. It assumes that dexamethasone is not inferior to prednisolone if the average PRAM score for dexamethasone at Day 4 is not more than one point higher than the prednisolone average PRAM score. On this basis, with a sample size of 232 subjects (105 in each group with a 10% loss to follow-up) we will be able to reject the null hypothesis - that the population means of the experimental and control groups are equal with a probability (power) of 0.9. The Type I error probability associated with this test (of the null hypothesis) is 0.05.

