**Methods/design:**

This is a randomized, non-inferiority, open-label clinical trial. After informed consent with or without assent, patients will be randomized to either oral dexamethasone 0.3 mg/kg stat or prednisolone 1 mg/kg/day for three days. The primary outcome measure is the comparison between the Pediatric Respiratory Assessment Measure (PRAM) across both groups on Day 4. The PRAM score, a validated, responsive and reliable tool to determine asthma severity in children aged 2 to 16 years, will be performed by a clinician blinded to treatment allocation. Secondary outcomes include relapse, hospital admission and requirement for further steroid therapy. Data will be analyzed on an intention-to-treat and a per protocol basis. With a sample size of 232 subjects (105 in each group with an estimated 10% loss to follow-up), we will be able to reject the null hypothesis - that the population means of the experimental and control groups are equal with a probability (power) of 0.9. The Type I error probability associated with this test (of the null hypothesis) is 0.05.

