### Data analysis

Data will be analyzed on an intention-to-treat and a per protocol basis. Data will be presented as means with standard deviations and Student’s *t* test will be used to compare differences in proportions between the groups. Significance will be set at the 5% level. No interim evaluation of the data is planned.

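### The stated null hypothesis, power and Type I error belong to a test of equal means, which contradicts the non-inferiority aim and the one-point margin; the sample size need not change

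*Protocol article*

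**What the plan says.** The protocol article is consistent about its purpose. The abstract declares the design: "This is a randomized, non-inferiority, open-label clinical trial". Statistical considerations gives the aim: "The aim of this study is to demonstrate that a single dose of dexamethasone is clinically non-inferior to a three-day course of prednisolone". The abstract's background and Study aims say the same.

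Sample size and power supplies a margin with a direction and a time point. Dexamethasone counts as not inferior if the "average PRAM score for dexamethasone at Day 4 is not more than one point higher than the prednisolone average PRAM score".

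The same section then says that with 232 subjects "we will be able to reject the null hypothesis - that the population means of the experimental and control groups are equal", with a power of 0.9, and that the Type I error of this test is 0.05. The abstract carries the same statement. Neither place says whether 0.05 is one-sided or two-sided.

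Data analysis plans intention-to-treat and per protocol analyses and a Student's t test, which it describes as comparing proportions. It adds: "Significance will be set at the 5% level". It does not connect the test to the one-point margin.

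**The concern.** In a non-inferiority trial the hypothesis to be rejected is that the new treatment is worse by at least the margin. The article names a different one, equality of means. Rejecting equality shows that the arms differ. It does not show that dexamethasone is less than one point worse. Failing to reject equality does not show that either.

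Two things are at stake. The stated power describes the chance of finding a difference, whereas the trial hopes to exclude one. And an analyst who followed the text literally would have a test whose non-significant result could be mistaken for success, with an error rate for the non-inferiority claim that nobody has fixed.

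**Working it through.** **Inputs.** From Sample size and power: margin 1 point; SD 2.23 at discharge and 1.5 at triage; power 0.9; Type I error 0.05; 105 per arm; 10% loss; 232 in total. Allocation is 1:1 (Patient randomization). The article does not say which SD was used and gives no Day 4 SD. It does not state the assumed true difference, which is taken as 0 for non-inferiority power, with other values shown below.

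**Reproducing the plan's figure.** n per arm = 2 × (z_alpha + z_power)² × SD² / margin².

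- Two-sided 0.05 (one-sided 0.025), SD 2.23: 2 × (1.960 + 1.2816)² × 2.23² / 1² = 104.5, so 105. This matches.
- One-sided 0.05, SD 2.23: 2 × (1.645 + 1.2816)² × 2.23² = 85.2, so 86. No match.
- SD 1.5: 48 (two-sided) or 39 (one-sided). No match.
- Loss to follow-up: 105 × 1.10 = 115.5, so 116 per arm and 232 in total. This matches.

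So the calculation used SD 2.23 and two-sided 0.05. A test of non-inferiority with margin 1, true difference 0, one-sided 0.025 and 90% power also gives 105 per arm. The two sample sizes coincide because the margin equals the difference to be detected.

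**What each test delivers at 105 per arm.** SE = 2.23 × √(2/105) = 0.308.

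| True difference (dexamethasone minus prednisolone) | Chance of rejecting equality, two-sided 5% | Chance that the upper 95% limit is below 1 |
|---|---|---|
| 0 | 5.0% | 90.1% |
| 0.25 | 12.8% | 68.3% |
| 0.5 | 36.9% | 36.9% |
| 1.0 | 90.1% | 2.5% |

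The columns mirror each other. The stated 90% holds for the stated null only at a full-point difference, which is the margin itself when dexamethasone is the worse drug.

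**Observed differences.** The half-width of the 95% interval is about 0.61. Equality is rejected once the observed difference exceeds about 0.61 in either direction. Non-inferiority needs an observed difference below about 1 − 0.61 = 0.39. Between 0.39 and 0.61 the t test is not significant, yet non-inferiority is not shown. For example, an observed 0.50 has an interval of about −0.11 to 1.11.

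**If non-significance were read as non-inferiority.** For a drug truly one point worse, the chance of a non-significant result is one minus the power to reject equality at a difference of 1:

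- SD 2.23: 1 − 0.901 = 9.9%.
- SD 1.5: 1 − 0.998 = 0.2%.

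The margin-based test holds this error at 2.5%.

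**The case against.** The strongest defence is that the margin, its direction and the time point are all stated, that the sample size is said to follow from them, and that 105 per arm is the right number for the non-inferiority test at one-sided 0.025. On this view the equality sentence is a slip in wording. The part about the sample size stands. The part about wording does not remove the problem, because the article defines its power and its Type I error by that sentence, in two places, and no other section corrects it.

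It is also fair to say that a journal article condenses the protocol and that an analysis plan may hold the decision rule. The absence of a confidence-limit rule is therefore not the finding. The finding is the null hypothesis that is stated and that contradicts the aim.

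A reader might go further and infer three things that the document does not support:

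- *That the planned test cannot show non-inferiority at all.* A significant result in favour of dexamethasone would imply it.
- *That the plan intends to treat a non-significant result as non-inferiority.* It nowhere says so. The 9.9% is conditional on that reading and depends on the Day 4 SD. At SD 1.5 the figure falls below 2.5%.
- *That a significant difference inside the margin would be a wrong conclusion.* It can coexist with non-inferiority.

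The unstated sidedness is minor, since the sample size points to one reading.

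**Conclusion.** The point holds as a contradiction in the current text. The null hypothesis, power and Type I error are stated for a test of equality, while the aim and margin are those of a non-inferiority trial. With SD 2.23 and 105 per arm, the probability of rejecting the stated null under equal effects is 5%, not 90%. The intended 90% is the probability of excluding a one-point deficit when the true difference is 0. A non-significant t test would not establish non-inferiority. The error from reading it that way would be about 9.9% at SD 2.23 and about 0.2% at SD 1.5, so its size cannot be fixed from the document. These figures rest on a normal approximation. The one-sided level of 0.025 is inferred from the sample size and is not stated. The sample size is not in question here.

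**What to change.** Make a dated amendment before the analysis starts. Trial Status says that recruitment ended in July 2012 and that analysis begins in September 2012. Because the trial is open-label and recruitment is complete, the date should be on record.

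- **Abstract and Sample size and power:** replace the equality statement. H0: mean Day 4 PRAM (dexamethasone) minus mean Day 4 PRAM (prednisolone) ≥ 1; H1: the difference is < 1; one-sided level 0.025; 90% power at a true difference of 0 with SD 2.23 and 105 per arm. The sponsor should confirm that one-sided 0.025 was the intended level, since one-sided 0.05 would have needed only 86 per arm.
- **Data analysis:** state that the primary conclusion rests on the upper limit of the two-sided 95% confidence interval for the mean difference being below 1, reported for both the intention-to-treat and the per protocol sets already planned.

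The cost is the amendment and its approval. No further patients or data are needed.
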